
### Participants

The sample will be obtained from among all patients with depression who have attended and are registered in the five mental health centres in the Recoleta area.

#### Inclusion criteria for families

Patients will be eligible if they are currently undergoing a depressive episode or if they have done so in the past 3 months. Eligible patients must have at least one non-depressed child between the ages of 6 and 12 years. In families in which only one parent has a depressive disorder, this parent will be the “identified parent” (IP) and the parent who does not have a disorder will be the “unidentified parent”. If both parents have depression, the parent with the most severe or chronic mood disorder will be designated as the IP.

#### Exclusion criteria

The following are the exclusion criteria for parents:Alcohol or drug dependence or abuse as assessed with the M.I.N.I., or being in treatment for substance usePsychosis, personality disorder, bipolar disorder or suicide ideation as assessed with the M.I.N.I.Having a relationship crisis with a current partner, assessed by self-report or by having attended couple’s therapy in the past monthAttending family therapy

The following are the exclusion criteria for children:Being outside the age range of 6–12 years at the time of recruitmentInability to understand or answer age-appropriate questionnaires (due to intellectual disability or otherwise)Having depression as assessed with the M.I.N.I.-KidBeing in treatment for or having taken psychotropic medication in the last month

#### Therapist recruitment

The people recruited to carry out the intervention will be psychologists and social workers in the different health centres as well as in schools within this catchment area. They will undergo a total of 9 h of training with a final assessment as an indicator of their abilities. It is expected that 20–25 people will be successfully trained in the intervention.

#### Sample size calculation

Despite the fact that a power calculation is not fully appropriate for a feasibility study [48], we have estimated a suitable number of children for this study. We expect that the proportion of children who will develop depressive symptoms within 1 year in the waiting-list control group will be 0.33, compared with 0.05 for those children in the intervention arm. For a loss to follow-up calculated at 15 % and in a two-sided contrast analysis, 32 children will be required per arm and 64 children in total. Despite there being evidence to support a one-sided analysis for this case, since we assume the intervention will not cause harm, we will carry out a two-sided analysis as is common in RCTs. This number is adequate according to recommendations for feasibility studies which propose a minimum of 30 participants per arm to estimate parameters for future sample size calculations [49, 50].

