## Background

Major depression is a prevalent and disabling condition that constitutes an important public health problem in Chile. This growing problem has been identified by numerous organizations as a major health-care priority in the country [1].

In the Chilean population, depressive disorders represent the second leading cause of specific disease [2]. Its prevalence, according to the latest national health survey, is 17.2 %, and is higher in women with fewer than 8 years of education [3]. More than 30 % of women consulting in primary health care have a diagnosis of depression. It is the second leading cause of disability in Chilean women, as measured by disability-adjusted life-years, and the fourth leading contributor to the global burden of disease [4, 5]. This disorder leads to greater disability than other chronic diseases, such as hypertension and diabetes, and explains over 40 % of sick leaves [1].

Depression is not a problem that affects only adults. In fact, 8 % of adolescents in Chile have major depression at any given time, and the lifetime prevalence of depression is 14 % [6]. Using the Beck Depression Inventory-II (BDI-II), researchers in a study in the city of Concepción found that 32.6 % of 746 secondary school students had depressive syndrome [7].

One of the most important risk factors for childhood depression is being the child of a depressed parent [6]. In fact, by age 20, a child with an affectively ill parent has a 40 % chance of having an episode of depression, and by age 25, this rate increases to 60 % [8]. These rates are two to four times higher than rates among their counterparts from homes without parental illness [9, 10]. Having a parent with depression is also associated with an increased risk of anxiety disorders and a variety of other problems, including poor health and deficits in academic performance, social relationships and self-esteem [10, 11].

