One possible environmental mechanism for the transmission of depression from parent to child is the quality of the parenting that the child receives [12, 13]. Parental depression negatively affects caregiving, material support and nurturance. Observational studies have documented numerous parenting difficulties among depressed mothers, including increased hostility, higher rates of negative interactions and impatient use of directives in guiding their children’s behaviour [13–15]. In other studies, depressed mothers have been found to be less responsive to their children’s behaviour, to communicate less effectively, to demonstrate lower synchrony with their infants, and to have fewer positive interactions with their children [16, 17]. In turn, quality of parenting has been found to be related to depression in children and adolescents (see [18] for a meta-analysis).

All of this, coupled with the fact that there is a big gap between the population of adolescents in Chile who manifest some form of mental health disorder and the population of adolescents who ultimately receive treatment, creates a very large need for preventive strategies.

*Prevention* refers to interventions before the onset of a disorder that are designed to prevent the disorder’s occurrence [19]. Preventive strategies are aimed at reducing the incidence, prevalence and recurrence of mental disorders; the time spent with symptoms; the risks for such mental illnesses; and the effects of illness on affected people, their families and society [20]. Recent efforts to develop preventive interventions for depression have been successful and suggest that depression is amenable to a public health approach to disease prevention [21, 22]. A preventive approach to mental illness is not only desirable but feasible and, according to a recent meta-analysis, also cost-effective [23].

To date, mental health interventions for depression have been focused almost exclusively on an individual treatment approach, but selective preventive interventions that are targeted at community individuals or groups demonstrating a higher than average risk have a strong evidence base [24]. A recent meta-analysis by Siegenthaler and colleagues of randomised controlled prevention trials showed that, in children of parents with a mental disorder, the risk to offspring for the same mental disorder was reduced by 40 % [25].

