#### Quantitative data analysis

Data presentation and results will be carried out according to Consolidated Standards of Reporting Trials (CONSORT) guidelines for RCTs. An ‘intention-to-treat’ basis will be used for the analysis of all participants allocated to the study groups. Initially, a descriptive analysis of the sample will be performed. The variables will be summarized at the different time points to evaluate any changes. To evaluate the changes produced by the intervention in the different treatment groups, and on variables of a continuous nature, two-way analysis of variance will be conducted. The independent variables will be ‘time’ (pre- vs. post-treatment) and ‘group’ (intervention group vs. control group). Other exploratory analyses will be carried out to see which variables have an effect on the outcome. Logistic regression analyses will be used to adjust for predictor variables of a dichotomous outcome, such as presence or absence of psychopathology, whereas linear regression analyses will be conducted to determine the effects of predictors on the continuous variables, such as family functioning. A sensitivity analysis will be conducted to investigate the potential effects of incomplete or missing data.

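### The claim that 32 children per arm is adequate holds for enrolled children only: the plan's own 15% loss leaves about 27 with final outcome data, and the number rests on an unsourced 85% risk reduction

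*Protocol article*

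**What the plan says.** The Sample size calculation section first concedes that a power calculation is not fully appropriate for a feasibility study, then gives one. It expects that "the proportion of children who will develop depressive symptoms within 1 year in the waiting-list control group will be 0.33, compared with 0.05" in the intervention arm. With 15% loss to follow-up it concludes that "in a two-sided contrast analysis, 32 children will be required per arm", 64 in total. Alpha and power are not stated, and neither rate has a source in that section. The section then calls the number adequate because recommendations for feasibility studies "propose a minimum of 30 participants per arm to estimate parameters for future sample size calculations".

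Two other places bear on this:

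- The Background reports a meta-analysis of randomised prevention trials in children of parents with a mental disorder, in which "the risk to offspring for the same mental disorder was reduced by" 40%.
- Under Quantitative data analysis, "Logistic regression analyses will be used to adjust for predictor variables of a dichotomous outcome", with presence or absence of psychopathology as the example.

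The Follow-up section sets the last assessment at 11 months after baseline.

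**The concern.** The section makes two claims for the same number: that it is required to detect the stated difference, and that it is enough to estimate parameters for a later trial.

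The claim about estimation compares 30 with the count before loss, although the same paragraph expects to lose 15%. Outcome parameters at 11 months, such as an event proportion or a standard deviation, can come only from children who are still being assessed.

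The claim about detection depends on an effect about twice as large as the only preventive effect that the article quantifies.

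The primary outcomes, acceptability and feasibility, do not depend on either claim. At stake is how the secondary results are read and carried forward. A null comparison could be taken as lack of benefit, a chance difference could be taken as proof, and the definitive trial could inherit both an optimistic effect and an overstated evaluable sample.

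**Working it through.** **Inputs.** From the Sample size calculation section: control 0.33, intervention 0.05, loss 15%, two-sided, 32 per arm, cited minimum 30 per arm. From the Background: 40% relative reduction. Assumed, because not stated: alpha 0.05 and power 0.80.

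**1. Reproducing the 32.** The unpooled normal approximation is

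n = (1.96 + 0.8416)² × (p₁q₁ + p₂q₂) / (p₁ − p₂)²

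= 7.849 × (0.33 × 0.67 + 0.05 × 0.95) / 0.28² = 26.9, so 27.

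Allowing for loss: 27 / 0.85 = 31.8, so 32. The plan's figure is matched exactly, and on these assumptions it was built for 27 completers per arm. Other two-sided formulas at 80% power give 31 (arcsine), 36 (pooled variance) or 44 (continuity-corrected) after loss.

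**2. Evaluable children against the cited 30.** 32 × 0.85 = 27.2, about 27 per arm or 54 in total. Keeping 30 after loss would take 30 / 0.85 = 35.3, so 36 per arm.

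**3. The assumed effect.** 1 − 0.05/0.33 = 0.848, an 85% relative reduction. This is 2.1 times the 40% in the Background.

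**4. Power with 27 evaluable per arm.** This enumerates both binomial distributions, two-sided 5%.

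| Rates | Fisher's exact | Uncorrected chi-square |
|---|---|---|
| 0.33 vs 0.05 (plan) | 65% | 82% |
| 0.33 vs 0.198 (40% reduction: 0.33 × 0.6) | 12% | 21% |

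For 80% power at 0.33 vs 0.198, the unpooled formula gives 7.849 × (0.33 × 0.67 + 0.198 × 0.802) / 0.132² = 171.1, so 172 evaluable per arm.

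**5. Events under the plan's own rates.** Control: 27 × 0.33 = 8.9. Intervention: 27 × 0.05 = 1.35. The total is about 10. The chance of no event in the intervention arm is 0.95²⁷ = 25%, or 0.95³² = 19% if nobody is lost. With no event in one arm, ordinary logistic regression has no finite estimate of the treatment effect, and about 10 events cannot support adjustment for several predictors.

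**6. What 64 children can estimate.** If 54 of 64 are retained, the proportion is 84%, with Wilson 95% CI 74% to 91%. This treats children as independent.

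**The case against.** The strongest reply is that this is a pilot. The Design section calls it primarily exploratory, and the Sample size calculation section itself plays down the power calculation. No efficacy decision depends on the test. That stands, and it limits the consequence to a weak justification and imprecise planning estimates.

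The cited minimum refers to participants, without saying enrolled or evaluable. If it means enrolled, 32 meets it, and recruitment and retention do use everyone enrolled. The loss of precision from 30 to 27 is also small: √(30/27) = 1.05, a confidence interval about 5% wider. This too stands, so the text does not support saying outright that the plan fails the rule. The adequacy claim needs limiting, because its stated purpose is to estimate parameters and some of those need final outcome data.

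A reader might infer four stronger points that the document does not support:

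- **That 32 is an arithmetic error.** It reproduces exactly with conventional alpha and power, and an article may leave those to the full protocol. The formula is not shown to mislead either: exact power of the uncorrected chi-square test at 27 per arm is 82%, and no test is named.
- **That 85% contradicts the cited 40%.** The 40% concerns the same mental disorder in offspring of parents with any mental disorder. The plan's outcome is depressive symptoms in children of depressed parents. The 40% is a benchmark only.
- **That a one-year rate of 0.33 is refuted by the Background statement that "by age 20, a child with an affectively ill parent has a" 40% chance of a depressive episode.** Symptoms and episodes differ. The Background also reports depressive syndrome in 32.6% of 746 secondary school students. That is a prevalence in older pupils and is not given as the source of 0.33, but it shows that symptom rates can run far above episode rates.
- **That the binary outcome was left out of the plan.** Child depressive symptoms on the CDI are a listed secondary outcome, and a cut-off is commonly left to the analysis plan.

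Finally, the logistic regression follows the mention of exploratory analyses and is not tied explicitly to the outcome used for sizing. Applying the 10 expected events to it is an inference, so the advice on method is conditional.

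**Conclusion.** The point holds in limited form. By the plan's own loss rate about 27 children per arm, not 32, would have outcome data at 11 months. The appeal to 30 per arm is sound for parameters measured on all enrolled children and unsupported for final outcome parameters. The calculation behind 32 is correct on assumed two-sided 5% alpha and 80% power, but it depends on an unsourced 85% reduction. Under the 40% benchmark, power would be about 12% to 21% depending on the test, so efficacy comparisons cannot be conclusive. The benchmark figures take 0.33 as the control rate and carry the 40% across to a different outcome and population. The justification should be corrected, but the primary feasibility and acceptability outcomes are unaffected.

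**What to change.** Reword the Sample size calculation section, keeping 64 children:

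- State that about 27 per arm are expected to be evaluable at 11 months, below the cited 30, and limit the adequacy claim to parameters measured on all enrolled children.
- Label 0.33 vs 0.05 as optimistic or give its source. Report power of about 12% to 21% under a 40% reduction as a benchmark, and say that efficacy comparisons are not conclusive.
- Justify 64 by the precision of feasibility parameters, for example 54/64 retained = 84%, 95% CI about 74% to 91%. Families are randomised and need at least one eligible child, so allow for siblings if a family contributes more than one.
- If the binary child depression outcome is analysed, report a risk difference with an exact confidence interval, or use Firth-penalised logistic regression with few covariates.

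The cost is protocol wording and one analysis choice. The stated figures become less favourable, and no additional families are needed.

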#### Randomisation

Once the family is fully enrolled and baseline evaluations are completed, the family will be randomised to either the intervention arm or a waiting-list group by a collaborator who will be blind to all evaluation outcomes and will conceal the allocation sequence until the intervention is assigned. The randomisation will be done with the use of a random number generator and will be stratified by health centre catchment areas. The use of block randomisation means that the intervention can be delivered in a staggered manner, with some participants beginning the intervention while further recruitment continues.

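### Families are randomised, but the target is counted in children and the stated models have no family term: if siblings are enrolled, precision for the secondary child outcomes is overstated

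*Protocol article*

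**What the plan says.** The relevant statements stand in four sections of the protocol article.

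- **Sample size calculation.** The count is of children: "we have estimated a suitable number of children for this study". The assumed risk of depressive symptoms within a year is 0.33 under waiting list and 0.05 under the intervention. With a two-sided test and an allowance of 15% for attrition, the section arrives at its target: "32 children will be required per arm and 64 children in total". No number of families is given, and neither a design effect nor a within-family correlation is mentioned.
- **Randomisation.** After baseline, "the family will be randomised to either the intervention arm or a waiting-list group".
- **Inclusion criteria for families.** "Eligible patients must have at least one non-depressed child between the ages of 6 and 12 years". There is no upper limit and no rule for picking one child when several qualify. The exclusion criteria for children apply to each child separately.
- **Quantitative data analysis.** Continuous outcomes go into a two-way ANOVA whose only factors are time and group. Logistic regression is named for dichotomous outcomes, and "linear regression analyses will be conducted to determine the effects of predictors on the continuous variables". None of these is described with a family term or a variance that allows for clustering.

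**The concern.** Siblings share a home, a depressed parent and, by design, a trial arm. Their depressive symptoms, behaviour scores and resilience scores are likely to be positively correlated. When the family is allocated and several of its children are analysed as separate observations, the comparison between arms has less information than the number of children suggests. A model with only time and group gives standard errors that are too small, intervals that are too narrow and tests that reject too often.

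The child count is also supported in the article by a rule of at least 30 participants per arm for estimating planning parameters. If siblings enter, 32 children are fewer than 32 independent units, and that margin can disappear. The outcomes at stake are the secondary child outcomes, not acceptability or feasibility.

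**Working it through.** **1. Reproduce the stated size.** Inputs from the Sample size calculation section: control risk 0.33, intervention risk 0.05, two-sided test, 15% loss. Alpha and power are not given; 0.05 and 0.80 are assumed.

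n = (z₀.₉₇₅ + z₀.₈₀)² × [p₁(1−p₁) + p₂(1−p₂)] / (p₁−p₂)²

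= (1.960 + 0.842)² × (0.2211 + 0.0475) / 0.28² = 26.9, rounded up to 27.

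27 / 0.85 = 31.8, rounded up to **32 per arm**, as stated. The arcsine formula also gives 27 and then 32. The pooled-variance formula gives 30 and then 36, and with continuity correction 37 and then 44. So on these assumptions 32 is the size for independent children, with a design effect of 1.

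**2. Allow for siblings.** The article gives neither the mean number of eligible children per family (m) nor the sibling ICC. The assumed ranges are m = 1.25 to 2 and ICC = 0.2 to 0.5. Formulas:

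- design effect DE = 1 + (m − 1) × ICC
- completers per arm = 32 × 0.85 = 27.2; effective completers = 27.2 / DE
- actual size of a nominal 5% test that ignores the family = 2 × P(Z > 1.96/√DE)
- children needed per arm = 26.9 × DE / 0.85, rounded up
- power from the unpooled formula in step 1, at the effective number of completers

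| m | ICC | DE | Effective completers per arm | True / naive SE | Size of nominal 5% test | Power | Children needed per arm | Families that 32 children represent |
|---|---|---|---|---|---|---|---|---|
| 1 | any | 1.00 | 27.2 | 1.00 | 5.0% | 80% | 32 | 32 |
| 1.25 | 0.2 | 1.05 | 25.9 | 1.02 | 5.6% | 79% | 34 | 25.6 |
| 1.5 | 0.3 | 1.15 | 23.7 | 1.07 | 6.8% | 75% | 37 | 21.3 |
| 2 | 0.5 | 1.50 | 18.1 | 1.22 | 11% | 63% | 48 | 16 |

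The power column assumes that the analysis allows for the family.

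**3. Unequal family sizes.** The formula treats every family as having m children. If half the families give one child and half give two (mean 1.5), the size-weighted mean is (1² + 2²)/(1 + 2) = 1.67. At ICC 0.3, DE is then 1 + 0.67 × 0.3 = 1.20 rather than 1.15, and the test size is about 7.4%. The rows with fractional m are therefore slightly optimistic.

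**4. Sparse events.** At the planned risks, 27.2 completers give about 0.05 × 27.2 = 1.4 events in the intervention arm and 0.33 × 27.2 = 9.0 in the control arm. A family random effect in a logistic model could hardly be estimated from so few events, which matters for the choice of remedy.

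**The case against.** The strongest reply is that the article never says siblings will be enrolled. The inclusion criterion is a condition on the parent, not an instruction to recruit every eligible child, and the Secondary outcomes section refers to the child in the singular. The exclusions (age, current depression, treatment or recent psychotropic medication, inability to answer) narrow the number of eligible siblings further. With one child per family the mismatch of units is harmless. This stands, and it makes the statistical consequence conditional.

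Three stronger readings are tempting but not supported:

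- **That siblings are in fact analysed as independent.** The statement that each child is interviewed belongs to the background description of the programme. It concerns a therapeutic interview, not enrolment or outcome assessment in this trial.
- **That the primary outcome rests on an inflated sample.** The Qualitative measures section already counts recruitment and completion in families. The 64 children are not used there as a denominator.
- **That two parents per family create the same problem in parent scores.** The depression inventory is listed for the parent in the singular, and one identified parent is designated even when both are depressed. Analysis of both parents is only an inference.

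It can also be said that the trial is an exploratory pilot, that the article itself plays down the power calculation, and that an unseen full protocol or analysis plan may deal with clustering. These points limit the weight of the concern. They do not remove it, because the article does commit itself to a count in children and to an ANOVA with named factors, and applied as written to siblings that analysis would be wrong.

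**Conclusion.** The point holds in conditional form. It is established that families are allocated, that the target is in children, that on the usual alpha and power 32 per arm contains no design effect, that nothing limits a family to one child, and that the stated models have no family term. It is not established that siblings enter.

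If they do, the distortion over the assumed ranges runs from negligible (design effect 1.05, test size 5.6%) to material (1.5, 11%). The upper end needs an average of two eligible children per family and an ICC of 0.5. At a mean of 1.5 and an ICC of 0.3, the shortfall is 37 − 32 = 5 children per arm. All these figures rest on assumed values, and the effect is confined to the secondary child outcomes. It should still be settled, because the remedy is cheap and does no harm if each family turns out to give one child.

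**What to change.** Choose one of two rules and state it.

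1. **Index child.** One eligible child per family enters the analysis, chosen at random before the family is randomised. The stated models then need no family term.
2. **All eligible siblings.** Add a family random intercept, or cluster-robust standard errors with a small-sample correction, to the child-outcome models. For sparse binary outcomes such as onset of depression, analyse the index child instead.

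Under either rule, express the 32 per arm in families as well as in children. If siblings enter, the sibling ICC may be reported for the definitive trial, but from about 64 children it will be imprecise and should be labelled descriptive.

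The cost is a change of wording and, under the second rule, slightly wider intervals. No extra data are needed.
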